**I. Study Background**

Cervical cancer is currently the third most common malignancy and the fourth leading cause of cancer-related death among women worldwide, posing a significant threat to women's health [1]. Globally, there are approximately 529,000 new cases and 275,000 deaths annually [2]. Over 80% of cervical cancer cases occur in developing countries. In China, there are approximately 130,000 new cases and 20,000 deaths annually, with recent trends indicating regional increases in incidence and earlier onset of the disease [3-5].

The optimal treatment strategy for cervical cancer depends on factors such as patient age, tumor stage, pathological type, fertility requirements, comorbidities, and institutional resources. Therefore, a comprehensive evaluation and multidisciplinary team discussion are essential to formulate individualized treatment plans, including surgery, radiotherapy, or chemoradiotherapy.

For early-stage cervical cancer (Stage I–IIA2), radical surgery and radical radiotherapy yield comparable outcomes, with similar 5-year survival, mortality, and complication rates. For bulky tumors (e.g., IB3 or IIA2), the NCCN guidelines prioritize radical radiotherapy (Category 2B recommendation for radical surgery), while in China, treatment decisions are tailored based on institutional surgical expertise and radiotherapy capabilities. Postoperative adjuvant concurrent chemoradiotherapy is recommended for patients with high-risk recurrence factors (parametrial invasion, positive vaginal margins, or lymph node metastasis). For intermediate-risk factors (tumor size, lymphovascular space invasion [LVSI], depth of

stromal invasion, based on Sedlis criteria), adjuvant radiotherapy ± chemotherapy is advised to reduce pelvic recurrence and improve survival. The Gynecologic Oncology Group (GOG) has established indications for postoperative radiotherapy:

| Lymphovascular Space Invasion | Cervical Stroma Invasion | Tumor Size (cm) |
|-------------------------------|--------------------------|-----------------|
| +                             | Deep 1/3                 | Any size        |
| +                             | Middle 1/3               | ≥ 2             |
| +                             | Superficial 1/3          | ≥ 5             |
| -                             | Middle or Deep 1/3       | ≥ 4             |

If any of the above criteria are met, postoperative adjuvant radiotherapy is recommended. The radiotherapy field should minimally include the vaginal stump 3-4 cm downward, parametrial tissue, and adjacent lymph node beds (e.g., external iliac and internal iliac lymph nodes). If common Iliac lymph nodes and paraaortic lymph nodes metastasis is confirmed, the upper boundary of the radiation field should be extended accordingly. Standard fractionation radiotherapy is typically recommended, with a dose of 45-50 Gy. For non-resectable enlarged lymph nodes, a dose of 10-15 Gy should be added using highly conformal external beam radiotherapy (EBRT). When using high-dose EBRT, particular attention should be paid to the radiation tolerance doses of normal tissues. External beam radiotherapy boost should be administered to areas where residual tumor may remain after surgery, to a total dose of approximately 60 Gy. For rare histological types such as adenocarcinoma, carcinosarcoma, and neuroendocrine carcinoma, which are less sensitive to radiotherapy, an appropriate increase in dose is recommended.

Previous studies have indicated that patients with adenocarcinoma of the cervix who undergo surgery followed by radiotherapy have a worse prognosis compared to those with squamous cell carcinoma or adenosquamous carcinoma, suggesting that adenocarcinoma is an independent poor prognostic factor. Moreover, patients with adenocarcinoma and lymph node metastasis have an even worse prognosis [4]. Therefore, a "four-factor" model theory for adjuvant radiotherapy in cervical adenocarcinoma has been proposed, which includes: tumor diameter >3 cm, LVSI (+),

extracervical 1/3 stromal invasion, and histological type of adenocarcinoma. Guidelines recommend that adjuvant radiotherapy is beneficial for patient survival prognosis if any two of the above factors are present.

However, for patients with full-thickness or outer full-thickness stromal invasion after radical surgery, the current adjuvant radiotherapy approach is the same as for other patients with intermediate or high-risk factors. Deep stromal invasion of cervical cancer has already been identified as an intermediate-risk factor for recurrence in cervical cancer. Previous retrospective studies have also found that the depth of cervical tumor invasion is an important prognostic indicator for patients with cervical cancer. Several studies have reported a significant correlation between deep stromal invasion and pelvic lymph node metastasis [5-6]. Research using three-dimensional pathological assessment has shown that approximately 30-60% of clinically "early" tumors (Stage IB-IIA) in patients with cervical cancer exhibit subclinical or occult parametrial spread, which is significantly associated with pelvic lymph node metastasis [7-10]. However, previous studies have been limited to deep stromal invasion, and there are currently no clinical or pathological reports that consider full-thickness or greater involvement of cervical tumors as a high-risk factor for recurrence. A retrospective analysis of the clinical and pathological data of patients with early-stage cervical cancer after radical surgery found that cervical stromal invasion is an independent prognostic factor for 5-year overall survival (OS) and disease-free survival (DFS) [11]. In our clinical practice, we have observed that many patients who underwent radical surgery for cervical cancer have pathological findings indicating tumor involvement of the full thickness or greater of the cervix. Review of their preoperative imaging studies consistently shows varying degrees of tumor invasion into surrounding tissues. Therefore, we believe that these patients should be distinguished from those with only deep stromal invasion but not reaching the full thickness or greater during postoperative adjuvant chemoradiotherapy.

During external beam radiotherapy, the cervical lesion is generally not given an additional boost, and boosting only the lymph nodes is sufficient. Moreover, most

cervical squamous cell carcinomas are sensitive to radiotherapy, and tumors typically regress by approximately 50-75% during the mid-to-late stages of radiotherapy, at which point brachytherapy is added to achieve radical treatment for cervical cancer. However, for patients who have undergone radical surgery, the surgical margin is approximately 2-3 cm from the vaginal stump. If parametrial positivity is indicated, brachytherapy may not reach an effective distance. Therefore, for these patients who may have residual tumor, the conventional external beam radiotherapy dose of 45-50.4 Gy may not achieve a radical dose for the tumor. Hence, it is necessary to administer a simultaneous integrated boost to the tumor bed during external beam radiotherapy to 60 Gy.

Approximately 29-38% of patients with early-stage cervical cancer experience recurrence after surgery, and recurrent cervical cancer is challenging to treat, with a low 5-year survival rate [12]. Few studies have investigated the factors associated with recurrence in cervical cancer. Relevant literature reports that 75% of cervical cancer patients experience recurrence within 2 years of initial treatment, and the recurrence rate after treatment for invasive cervical cancer is 29%, with 35% of recurrences localized to the pelvis [13]. Currently, treatment for localized pelvic recurrences primarily involves surgery or radiotherapy. Due to the close proximity of the vaginal stump to the posterior wall of the bladder, postoperative pelvic adhesions, and vaginal wall fibrosis caused by postoperative radiotherapy, repeat surgery after recurrence is very difficult. The NCCN guidelines recommend a treatment plan of radiotherapy combined with chemotherapy for patients with recurrent cervical cancer [14]. Pelvic external beam radiotherapy and brachytherapy are crucial for reducing the risk of vaginal stump recurrence and improving overall survival in patients with Stage I-II cervical cancer after radical surgery. Patients with high-risk and intermediate-risk factors after surgery should be actively given adjuvant radiotherapy.

This study aims to evaluate the potential benefits of adjuvant chemoradiotherapy with a simultaneous integrated boost for patients with full-thickness or outer full-thickness cervical stromal invasion after radical surgery for

early-stage cervical cancer. By analyzing the survival outcomes of patients after treatment, this study seeks to assess and explore the clinical relationship between full-thickness or outer full-thickness stromal invasion and recurrence and survival prognosis, as well as the guiding significance of adjuvant therapy for such patients.

## **II. Research Content and Technical Key Points**

### **2.1 Research Objectives:**

This study aims to evaluate the potential benefits of adjuvant chemoradiotherapy with or without a simultaneous integrated boost in patients with early-stage cervical cancer who have undergone radical surgery and have full-thickness or outer full-thickness stromal invasion.

- **Primary Objective:** 3-year progression-free survival.
- **Secondary Objectives:** 3-year overall survival rate, acute and late toxicities, and progression patterns.

Progression-free survival (PFS): PFS is defined as time from randomization to first radiological/histopathological progression or all-cause death.

Overall survival (OS): Refers to the time period from the date of receiving study treatment to the date of death (any cause). Subjects without an observed death will be censored at the time of confirmed survival.

Acute and late toxicities: KPS score, vital signs, Physical examination, laboratory tests (blood routine examination, routine urine and stool test), comprehensive metabolic panel, coagulation test and so on), ECG, Cardiac ultrasound, adverse events (AEs), AEs is recorded based on CTCAE 5.0 criteria.

Progression patterns: Analyze the progression pathways of the disease, including local-regional recurrence (pelvic region/vaginal cuff/para-aortic nodes), distant metastasis (inguinal nodes, intra-abdominal sites, lungs, liver, bones), tumor bed boost local control (absence of recurrence within the contoured SIB volume)

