### 2.2.1 Study Design:

This is a single-center, randomized, Phase III trial.

- **Group A:** Standard adjuvant chemoradiotherapy + simultaneous integrated boost.
- **Group B:** Standard adjuvant chemoradiotherapy without simultaneous integrated boost.

All patients in both groups will receive standard pelvic external beam radiotherapy. Concurrent chemotherapy with cisplatin will be administered at a dose of 40 mg/m^2 weekly for 5 weeks.

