## 2.5 Main Research Content:

### 2.5.1 Radiotherapy

Radiotherapy must begin within 4 weeks after randomization.

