#### 2.5.1.2 External Beam Radiotherapy Technique:

- Patients are required to drink 500 ml of water one hour before simulation to ensure bladder fullness.
- CT simulation is performed with the upper boundary at the inferior edge of

278 T10 and the lower boundary at the vulvar opening, with 5 mm slice thickness.

279 • Radiotherapy is delivered using intensity-modulated radiation therapy (IMRT)  
280 techniques.

281 • The pelvic field CTV includes internal iliac, external iliac, common iliac,  
282 obturator, presacral, uterine cervix, corpus uteri, adnexal areas, parametrial  
283 tissue, part or all of the vagina, and the extended field CTV includes the pelvic  
284 field plus the para-aortic lymph node drainage area, with the upper boundary  
285 at the level of the left renal vein.

286 • Specific target delineation refers to the "Fudan University Shanghai Cancer  
287 Center Gynecological Oncology Target Delineation Guidelines."

288 • The PTV is expanded 0.8 cm from the CTV.

289 • Patients are required to drink 500 ml of water one hour before radiotherapy to  
290 maintain bladder fullness.

291 The upper boundary of the external beam plan is generally at the level of the  
292 aortic bifurcation, and the lower boundary is determined based on the extent of  
293 vaginal involvement. The target area must include the tumor bed, parametrium,  
294 uterosacral ligaments, presacral lymph nodes, and other potentially involved lymph  
295 nodes, as well as sufficient vaginal tissue. If common iliac or para-aortic lymph node  
296 metastasis has occurred, extended field irradiation is required, with the upper  
297 boundary reaching the level of the renal vessels or extended cephalad based on the  
298 lymph node involvement.

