#### **2.5.1.4 Simultaneous Integrated Boost:**

During the external beam target delineation process, the tumor bed area will be given a simultaneous integrated boost of 58.80 Gy/2 8 fractions. The upper boundary is 2 cm above the femoral head, the lower boundary is 2cm inferior to the vaginal cuff, the two laterally sides are the medial edge of the internal obturator muscle and the pubococcygeus muscle, the front boundary includes the posterior wall of the bladder, and the posteriorly boundary is the part where the residual sacral ligament and the rectal mesentery fuse with the sacral ligament.

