#### **2.5.7.2 Statistical Analysis Plan**

The statistical analysis plan (SAP) will be developed prior to database lock and will specify all analysis methods, including the primary and secondary outcome measures, subgroup analyses, and handling of missing data.

The SAP will be followed strictly during the analysis phase to avoid data - driven

analyses and ensure the integrity of the study results.

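### Tumor-bed control is scored inside a boost contour that the protocol calls for only in Group A, so as written it can describe Group A but cannot compare the arms

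*Protocol*

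**What the plan says.** Protocol section 2.1 makes progression patterns a secondary objective and names several components. One is "tumor bed boost local control (absence of recurrence within the contoured SIB volume"). Another, listed separately, is "local-regional recurrence (pelvic region/vaginal cuff/para-aortic nodes").

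Section 2.2.1 defines Group B as "Standard adjuvant chemoradiotherapy without simultaneous integrated boost".

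The boost region is described in section 2.5.1.4, where "the tumor bed area will be given a simultaneous integrated boost". Its limits are anatomical: "The upper boundary is 2 cm above the femoral head, the lower boundary is 2cm inferior to the vaginal cuff", with lateral, anterior and posterior limits set by muscle, bladder wall and ligament.

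Section 2.5.1.2, which applies to both arms, says "The target area must include the tumor bed, parametrium" and other structures. It does not bound the tumor bed or ask for it as a separate structure, and it refers delineation detail to an institutional guideline that is not shown.

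On timing, section 2.5.1 says "Radiotherapy must begin within 4 weeks after randomization", and section 2.5.7.2 says "The statistical analysis plan (SAP) will be developed prior to database lock". Section 2.5.4 calls for a CT at any recurrence to establish its pattern. Section 2.5.7.5.2 extends the comparative methods to secondary outcomes where suitable, without saying which ones are to be compared.

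**The concern.** The boost is meant to act in the tumor bed, so recurrence there is the most direct measure of what it does. An outcome tied to the boost contour has a defined region in Group A. In Group B no boost is planned, and nothing shown requires the contour.

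This leaves two readings. If the item describes Group A only, there is no randomized comparison of in-bed control. If the arms are compared, someone has to supply a Group B region. Group A's region was fixed at planning. Group B's could be drawn once the recurrence CT has shown where the tumor came back. With few events, a small number of boundary decisions could shift the comparison.

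**Working it through.** **1. Does any text create the region in Group B?**

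| Protocol section | Applies to | What it provides |
|---|---|---|
| 2.1 | outcome definition | scoring inside the contoured boost volume |
| 2.2.1 | both arms | boost in Group A, none in Group B |
| 2.5.1.2 | both arms | bed lies within the target; no bounds, no separate structure |
| 2.5.1.4 | boosted volume | bounds on all sides, as part of giving the boost |

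No row asks for the contour in an unboosted patient. The limits in 2.5.1.4 do not depend on dose, however, so the same region can be placed on any planning CT. What is not fixed is that it be drawn in Group B, and when.

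**2. How many patients depend on the boundary?**

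The protocol gives no in-bed recurrence rate, so this is an illustration.
- From section 2.5.6: 233 per group; 3-year PFS 78% (A) and 65% (B).
- From the Study Background: 35% of recurrences are pelvic, a figure for treated invasive cervical cancer in general.
- Assumed: every PFS event is a recurrence; the same pelvic share applies in both arms; crude proportions without censoring.

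Pelvic recurrences = 233 × (1 − PFS) × 0.35:
- A: 233 × 0.22 × 0.35 = 17.9, about 18.
- B: 233 × 0.35 × 0.35 = 28.5, about 29.

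A patient without a pelvic recurrence counts as controlled wherever the line is drawn. In Group B about 29 classifications depend on it, not 233. If only 80% of events are recurrences, the counts are 14.4 (14) and 22.8 (23).

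**3. What would a comparison show under one scoring rule?**

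In-bed count = share × pelvic recurrences; control = 1 − count/233; two-sided Fisher exact test. The share is assumed.

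| In-bed share | Count A v B | Control A v B | Difference (points) | p |
|---|---|---|---|---|
| 25% | 4 v 7 | 98.3% v 97.0% | 1.3 | 0.54 |
| 50% | 9 v 14 | 96.1% v 94.0% | 2.1 | 0.39 |
| 100% | 18 v 29 | 92.3% v 87.6% | 4.7 | 0.12 |

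With 80% of events as recurrences, a 50% share gives 7 v 11 (p = 0.47) and 100% gives 14 v 23 (p = 0.17).

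**4. How sensitive is it to the Group B boundary?**

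One reclassified recurrence moves Group B control by 1/233 = 0.43 points. Take the 50% share and hold Group A at 9:
- moving 5 of Group B's 14 outside the line gives 9 v 9, and the difference disappears;
- moving 6 of the other 15 (29 − 14) inside gives 9 v 20, p = 0.053;
- moving 7 inside gives 9 v 21, p = 0.036.

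These shifts are all in one direction, and no document supports misclassification of that size. They show sensitivity only.

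**The case against.** The strongest reply is that the item is coherent as it stands. Its name and its definition both presuppose a boost, section 2.1 announces no between-arm test of it, and section 2.5.7.5.2 compares secondary outcomes only where suitable. Read as a description of Group A, it contains no error. That stands, and the point is limited accordingly.

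It can also be said that an unseen SAP may settle the matter. A SAP can decide whether the item is compared and how recurrences are scored. Even a late one could order outcome-blind contouring on the original planning CT, which would limit any bias. It cannot make the contour part of planning for patients already treated, and the latest date set for it is database lock. That date does not show that the SAP was in fact written late.

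The institutional guideline cited in section 2.5.1.2 might call for a separate tumor-bed structure in every patient. Nothing shown says that it does or does not.

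A reader might infer that the comparison of local effect is lost, or that Group B will be contoured with knowledge of outcome. The documents support neither. Locoregional recurrence, including pelvis and vaginal cuff, is defined for both arms. No text prescribes contouring after recurrence, and the fixed landmarks leave limited room for influence. Nor does the gap reach all 233 Group B patients.

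Finally, even with perfect contouring the illustrative comparison is underpowered (p from 0.12 to 0.54). That lowers the stakes.

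**Conclusion.** The point holds in limited form. On the text shown, tumor-bed control has a defined region only where a boost is given, so it can describe Group A but does not support a randomized comparison. A comparison would rest on a Group B region that nothing shown requires and whose timing is open.

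The weight is minor to moderate. This is one component of one secondary objective; the primary outcome, OS, the sample size and locoregional recurrence are untouched. The count of about 29 rests on the planned PFS rates, on all events being recurrences and on the 35% pelvic share (about 23 if 80% of events are recurrences). The in-bed share is not in the protocol. Confidence is medium, because the delineation guideline is not shown. The case for change is that the better rule is concrete and cheap, and that a contour made at planning cannot be recovered afterwards.

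**What to change.** - In sections 2.5.1.2 and 2.5.1.4, require the region bounded in 2.5.1.4 to be contoured on the planning CT in both arms before treatment, ideally before allocation is known, and boosted only in Group A.
- In section 2.1, define the outcome as absence of recurrence within that region in both arms.
- For Group B patients already planned, apply the same landmarks to the original planning CT without reference to the recurrence imaging, preferably by someone unaware of outcome. This can be limited to patients with a pelvic recurrence.
- If the item is meant for Group A only, label it descriptive and draw no between-arm conclusion from it.

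The cost is a wording change and one extra contour per Group B patient (at most 233) on a CT that already exists. Dose, sample size and primary outcome stay as they are.

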### **2.2 Innovativeness:**

This is the first randomized controlled Phase III clinical trial to investigate adjuvant chemoradiotherapy with or without a simultaneous integrated boost in patients with early-stage cervical cancer who have undergone radical surgery and have full-thickness or outer full-thickness stromal invasion.

### 2.2.1 Study Design:

This is a single-center, randomized, Phase III trial.

- **Group A:** Standard adjuvant chemoradiotherapy + simultaneous integrated boost.
- **Group B:** Standard adjuvant chemoradiotherapy without simultaneous integrated boost.

All patients in both groups will receive standard pelvic external beam radiotherapy. Concurrent chemotherapy with cisplatin will be administered at a dose of 40 mg/m^2 weekly for 5 weeks.

### 2.2.2 Study Population:

Patients who underwent radical surgery for cervical cancer at our center between October 2019 and October 2020, with postoperative pathology indicating full-thickness or outer full-thickness stromal invasion.

### 2.2.3 Randomization:

Patients will be randomized using a minimization method into two groups: standard adjuvant chemoradiotherapy with simultaneous integrated boost or standard adjuvant chemoradiotherapy without simultaneous integrated boost. Randomization will be performed using a random number table, with a 1:1 allocation ratio.

### 2.3.1 Inclusion Criteria:

1. Pathological confirmation of full-thickness or outer full-thickness stromal invasion after radical surgery for cervical cancer.
2. Age 18-65 years.
3. ECOG performance status 0-2.
4. Histological type: squamous cell carcinoma, adenocarcinoma, or adenosquamous carcinoma of the cervix.
5. WBC  $\geq 3.5 \times 10^9/L$ , ANC  $\geq 2.0 \times 10^9/L$ , platelets  $\geq 100 \times 10^9/L$ .
6. Bilirubin  $\leq 1.5 \times ULN$ , AST or ALT  $\leq 2.5 \times ULN$ .
7. Good renal function.
8. Signed informed consent.

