### **2.3.2 Exclusion Criteria:**

1. Postoperative pathology indicating parametrial involvement.
2. Patients who received chemotherapy before radiotherapy.
3. Bilateral hydronephrosis, inability to place ureteral stents, or inability to perform nephrostomy.
4. Distant metastasis.
5. History of ulcerative colitis or Crohn's disease.
6. Other active malignancies.
7. Pregnant or breastfeeding patients.
8. Contraindications to cisplatin chemotherapy.
9. Severe underlying medical conditions that preclude safe administration of study treatment, including but not limited to persistent or active infection, symptomatic congestive heart failure, unstable angina, arrhythmias, or psychiatric/social conditions that may limit adherence to study requirements.
10. HIV positive.

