#### **2.5.6 Sample Size and Feasibility Analysis:**

Based on the retrospective analysis data of our center, the estimated 3-year progression-free survival (PFS) for patients with FIGO stage IB, IIA, and IIIC cervical cancer following primary treatment was observed to be 65%. This investigation is designed to demonstrate a statistically significant 13% improvement in PFS, corresponding to an anticipated 3-year PFS rate of 65% in the control cohort compared to 78% in the experimental arm. Recruitment is expected to take 2 years, with a 3-year follow-up period. Utilizing a conventional significance level ( $\alpha$ ) of 0.05 and statistical power ( $1 - \beta$ ) of 0.9 ( $\beta = 0.1$ ), with a 5% anticipated attrition rate and 1:1 randomization scheme, sample size calculations determined a requirement of 211 cases per group. This determination was cross-validated through PASS 15, nQuery, and G\*Power statistical software.

Considering substantial variability in PFS rates reported across existing literature,

we implemented a 10% sample size augmentation strategy to enhance detection sensitivity for clinically meaningful differences, mitigate type II error risks, and improve result validity. This adjustment results in a revised minimum enrollment target of 233 participants per group, yielding an anticipated statistical power of approximately 95% for detecting the hypothesized treatment effect.

This study plans to enroll at least 466 patients with cervical cancer who have undergone radical surgery and have full-thickness or outer full-thickness stromal invasion. Fudan University Shanghai Cancer Center treats nearly 1,000 cases of cervical malignancies annually, including approximately 300 cases of radical radiotherapy and 600 cases of postoperative adjuvant radiotherapy. Thus, the hospital has sufficient capacity to complete the required number of cases for this trial. The Gynecological Oncology Department has been conducting intensity-modulated radiation therapy (IMRT) for cervical cancer since 2007 and has completed approximately 4,000 cases of IMRT for cervical cancer, demonstrating technical maturity. Additionally, the hospital's molecular pathology laboratory has mature detection techniques.

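### The objective is worded for early-stage disease, but the eligibility criteria, the treatment section and the planning rate all admit node-positive (IIIC) patients, and the protocol does not say how the label fits them

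*Protocol*

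**What the plan says.** - **Objective.** Protocol section 2.1 evaluates the boost "in patients with early-stage cervical cancer who have undergone radical surgery and have full-thickness or outer full-thickness stromal invasion". The end of section I and section 2.2 use the same early-stage label.
- **Meaning of the label.** Section I gives a range in passing: "For early-stage cervical cancer (Stage I–IIA2), radical surgery and radical radiotherapy yield comparable outcomes". No study definition is given elsewhere.
- **Eligibility.** Section 2.3.1 limits disease extent by "Pathological confirmation of full-thickness or outer full-thickness stromal invasion after radical surgery for cervical cancer". Neither 2.2.2 nor 2.3.1 names a FIGO stage, a staging edition or nodal status. Two exclusions in 2.3.2 bear on extent: "Postoperative pathology indicating parametrial involvement" and "Distant metastasis". Nodal metastasis is not excluded.
- **Treatment.** Section 2.5.1.2 has an extended-field provision that begins "If common iliac or para-aortic lymph node" and covers metastasis at those sites.
- **Planning rate.** Section 2.5.6 takes the 65% three-year control PFS from the centre's patients with "FIGO stage IB, IIA, and IIIC cervical cancer following primary treatment", then plans for 65% against 78%. Its enrolment sentence leaves out the early-stage label.

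**The concern.** Stage IIIC lies outside I–IIA2, yet the protocol uses IIIC patients to set its control rate and has no criterion that keeps them out. A final report that follows the objective would state a conclusion for early-stage disease. The data behind it could include an unstated share of node-positive patients. A reader could not tell whether the result applies to node-negative patients, to node-positive patients or to a mixture. The share may not be small: section I itself links deep stromal invasion with pelvic nodal metastasis.

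**Working it through.** **1. The passages side by side**

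| Place | Patients described | IIIC included? |
|---|---|---|
| 2.1 objective, with the gloss in section I | early-stage, I–IIA2 | No, if read as final stage |
| 2.3.1 and 2.3.2 | stromal invasion after radical surgery; no parametrial involvement, no distant metastasis | Yes |
| 2.5.1.2 | provision for common iliac or para-aortic metastasis | Yes |
| 2.5.6 | IB, IIA and IIIC | Yes, by name |

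Three of the four rows agree. Only the label differs.

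**2. Does the plan's own sample size reproduce?** Inputs: 65% against 78% at 3 years, alpha 0.05, power 0.90, 5% attrition, 2 years of recruitment plus 3 of follow-up (all 2.5.6); two-sided (2.5.7.10). Exponential PFS and uniform accrual are assumed.

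- Hazard ratio = ln 0.78 / ln 0.65 = 0.577.
- Event probability per arm = 1 − [exp(−3λ) − exp(−5λ)]/(2λ), with λ = −ln S(3)/3. This gives 0.435 and 0.281, mean 0.358.
- Schoenfeld: 4(1.960 + 1.282)²/(ln 0.577)² = 139 events. 139/(2 × 0.358) gives 195 per arm, and 195/0.95 gives 206.
- Freedman: (1.960 + 1.282)² × (1.577/0.423)² = 146 events, 204 per arm, and 204/0.95 gives 215.
- The stated 211 lies between 206 and 215. Then 211 × 1.10 = 232.1, rounded up to 233.
- Power at 233 per arm (Schoenfeld): 2 × 233 × 0.358 = 167 events, 94.5%. With 5% attrition, 159 events and 93.4%. The plan says about 95%.

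The plan does not name its method. A two-sided comparison of two proportions would give 266 per arm, so a time-to-event method is the likely one. On that basis the arithmetic is sound.

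**3. What follows if IIIC is not meant to be eligible.** The documents give no stage-specific PFS. Assume a control rate without IIIC of 70–80%, with the hazard ratio held at 0.577, 233 per arm and 5% attrition:

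| Control 3-year PFS | Events | Power | N per arm for 90% |
|---|---|---|---|
| 65% (as planned) | 159 | 93% | 206 |
| 70% | 136 | 90% | 238 |
| 75% | 114 | 84% | 285 |
| 80% | 92 | 75% | 354 |

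**4. What follows if IIIC stays eligible.** Assume a 30% IIIC share, IIIC control PFS of 35–45%, an overall rate still at 65%, and a common hazard ratio of 0.577. The remaining patients then have a control rate of (0.65 − 0.30 × 0.35)/0.70 = 77.9% down to (0.65 − 0.30 × 0.45)/0.70 = 73.6%. In simulation, an unstratified log-rank test has about 85–91% power, and one stratified by nodal status about 92–93%. The gain shrinks as the IIIC rate approaches that of the other patients.

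**The case against.** The strongest reply is that early-stage means clinical stage before surgery, with IIIC assigned afterwards from the surgical nodes. Section I supports this. Its early-stage discussion lists lymph node metastasis among postoperative risk factors, and it speaks of clinically early tumours in connection with nodal spread. The I–IIA2 range is also a background parenthesis, not a study definition. This reading is plausible and may well be the intended one. But the protocol never states it, and 2.5.6 uses IIIC as the stage label. So a clarification is still needed, though a claim that the wrong patients are being enrolled would go too far.

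A reader might also infer that there is no limit on stage at all. The documents do not support that: radical surgery is required, and parametrial involvement and distant metastasis are excluded. What is absent is a FIGO stage criterion and any nodal limit.

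A reader might further infer that IIIC patients dilute the planned effect. Suppose the 13 points belonged to I–IIA2 alone, IIIC were 30% of patients and gained half as much. The overall gain would then be 0.7 × 13 + 0.3 × 6.5 = 11.05 points and power 83%. With no gain in IIIC it would be 9.1 points and 65%. The arithmetic is right, but the premise is not in the plan. Section 2.5.6 sets the 13 points against a control rate that already includes IIIC, and the documents give neither a IIIC share, nor a smaller effect in IIIC, nor failure patterns by nodal status. Those losses are not a finding.

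Two smaller replies stand in part. The target-volume text in 2.5.1.2 lists the cervix and corpus uteri for patients after radical surgery, so it may be general departmental text and weak evidence of intent; the mismatch does not depend on it. Section 2.2.3 names no minimisation factors, and covariates can be left to the SAP, so the absence of nodal status there is not itself an error.

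**Conclusion.** The point holds as an inconsistency in the stated population. The eligibility criteria, treatment section and planning rate admit node-positive patients. The objective uses a label that the protocol glosses as I–IIA2 and never reconciles with them. The sample size for the population in 2.5.6 is not in error. The consequence is for what the trial can claim, and it is worth correcting because it decides which patients the conclusion names. The power figures for a trial without IIIC (about 90% down to 75%) rest on assumed control rates of 70–80% and an unchanged hazard ratio. The gain from stratifying (from about 85–91% to 92–93%) rests on an assumed 30% IIIC share, an assumed worse prognosis in IIIC and a common hazard ratio.

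**What to change.** Reconcile 2.1, 2.3.1 and 2.5.6 so that they name the same patients: eligible FIGO stages and edition, whether stage is clinical or pathological, and nodal status. Which population is intended is for the sponsor to state.

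- **If node-positive patients are eligible:** word the objective and the conclusion to match, for example clinically early-stage disease including pathological IIIC. Use pathological nodal status as a minimisation factor, and as a stratum or covariate in the primary PFS analysis. If allocation has already been made, only the analysis part can still be applied.
- **If they are not eligible:** say so in the criteria, bring 2.5.1.2 into line, take the control rate from the centre's data without IIIC, and restate the power.

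The cost is an amendment of wording, a less simple population label and slightly more analysis work. Nodal status should already be known from surgical pathology, so no new data collection is expected. The second option may also call for a larger sample if the control rate rises.
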